## Abstract

**Background:**

Among US teenagers, 79% of HIV infections are attributable to male-to-male sexual contact; yet, few interventions have been shown to effectively reduce sexual risk among gay and bisexual adolescents (GBA). Parent communication about sex is associated with adolescent sexual risk, and interventions to improve parent communication have been shown to successfully reduce sexual risk among heterosexual samples. However, no interventions designed specifically for parents of GBA have been tested in clinical trials. Parents and Adolescent Talking About Healthy Sexuality (PATHS) is a web-based intervention we created for parents of GBA that aims to improve parent communication about sexuality and HIV and increase parent behaviors supportive of GBA sexual health.

**Objective:**

This trial aims to test whether delivering PATHS to parents of GBA ages 14-19 years will improve GBA sexual health outcomes in the 6 months following intervention delivery. Secondary aims are to test whether the intervention’s effects are sustained at 12 months after the intervention and to examine whether effects are mediated through specific parent behaviors.

**Methods:**

In total, 350 parents of GBA will be recruited online via social media advertising and randomized to receive either PATHS or an active control. PATHS is fully automated, self-paced, and can be completed in a single session lasting under an hour. The active control is an education entertainment film created to provide general support and guidance to parents of GBA. Both parents and their GBA sons will complete online assessments every 3 months over a 1-year period. Primary outcomes will be evaluated at 6 months after the intervention, and then, the control arm will crossover and receive PATHS, and dyads will be followed for another 6 months. Primary outcomes include both adolescent sexual preparedness (eg, condom skills) as well as HIV-related sexual risk behavior (ie, condomless anal or vaginal sex that is not protected by pre-exposure prophylaxis).

**Results:**

The study was funded in March 2022, and we completed enrollment of 393 parent-GBA dyads in September 2025. We project that all participants will have completed study activities by November 2026, with data analysis and results of the trial forthcoming in the first quarter of 2027.

**Conclusions:**

If proven efficacious, PATHS will be among the first HIV prevention interventions shown to reduce sexual risk for GBA. Moreover, as other adolescent-focused interventions emerge, PATHS’ unique focus on parents will offer a complementary, additional means for reaching GBA who do not engage with other intervention options.

**Trial Registration:**

ClinicalTrials.gov NCT05852600; https://clinicaltrials.gov/study/NCT05852600

**International Registered Report Identifier (IRRID):**

PRR1-10.2196/81316

## Introduction

### Background

Youths aged 13-24 years accounted for 19% of new HIV infections in the United States in 2022 [1]. Young men who have sex with men (MSM) make up most of these infections: 82% of new infections among teens ages 13-19 years and 81% of infections among young adults ages 20-24 years [1]. Among young MSM, HIV is further concentrated in African American and Latino youths, who make up 49% and 32% of new infections, respectively [2]. HIV-infected youths are less likely than older individuals to know their HIV status and, as a result, are the group least likely to engage in the continuum of HIV care leading to viral suppression [3]. Less than a quarter of MSM aged 13-19 years have ever taken an HIV test [4,5].

Despite stark disparities in HIV incidence and testing, interventions to reduce sexual risk and increase HIV testing among young MSM remain extremely limited, particularly for MSM in their teens. While a handful of interventions for adolescent men who have sex with men (AMSM) are in various phases of development and testing, all of the emerging interventions we have identified use individual-level approaches to intervene directly with AMSM (eg, SMS text messages and web-based interventions) [6-9], leaving other levels of influence (ie, family, network, and community) largely unaddressed.

An abundance of research with predominantly heterosexual samples demonstrates that parent-adolescent communication about sex is related to various sexual health outcomes, including delayed initiation of sexual activity [10], as well as greater use of condoms [11-14], and other contraceptives [11,13-15]. Emerging research from our team suggests that this is true for AMSM as well [16,17]. Moreover, multiple interventions to promote parent-adolescent communication about sex have been developed and tested in samples comprised of parents of presumably heterosexual adolescents. A systematic review of these interventions found that they were effective at improving multiple dimensions of parent-adolescent communication [18]. In addition to improving communication, a 2019 meta-analysis found that the interventions also had overall positive effects on adolescent sexual health outcomes [19]. Although the positive effects of parent-focused interventions are now well-documented, we note 2 important limitations in this literature. First, none of the trials addressed sexual health outcomes in nonheterosexual youths. Second, we were unable to identify any published report that tested which specific parent behaviors mediated the effects of interventions on adolescent sexual health outcomes.

In response to the dearth of HIV prevention interventions for AMSM, including those with a parent-focus, we created Parents and Adolescents Talking About Healthy Sexuality (PATHS). PATHS is an online intervention delivered to parents of gay and bisexual adolescents (GBA) that aims to increase parent communication about sexuality and HIV as well as other parent behaviors supportive of sexual risk reduction. In a pilot randomized controlled trial (RCT), PATHS was shown to increase both parent and child reports of how much parents discussed HIV, provided instruction on condom skills, helped sons access condoms, and facilitated their sons in getting HIV tests [20].

### Objectives

Building on the promising effects PATHS had on parent behaviors, the goal of this trial is to test whether PATHS improves sexual health outcomes in GBA ages 14-19 years and to examine whether these effects are mediated through specific parent behaviors.

## Methods

### Ethical Considerations

All methods were evaluated for adequate protection of human participants as a part of the National Institutes of Health review process. They were also reviewed and formally approved by the George Washington University Institutional Review Board (NCR213761). All adult participants (parents and GBA ages 18 years and older) reviewed an online informed consent document and indicated their consent electronically. For GBA younger than 18 years of age, parents reviewed an online permission form and provided permission electronically, and their sons reviewed an online assent document and indicated their assent electronically. Participant privacy and confidentiality were maintained in a variety of ways (eg, by using secure online data collection tools; by separating data from identifiers and storing these in secure, password-protected files). Parents received a US $100 gift card after completing the first 3 study requirements: survey 1, engaging in the intervention, and completing survey 2. Parents then received a US $50 gift card after completing each additional assessment. Sons received a US $25 gift card after completing any study activity.

### Study Design

We are conducting an RCT of PATHS with a national sample of parent-GBA dyads recruited online (proposed n=350, 50% racial or ethnic minority). Parents will be randomized in a 1:1 ratio to receive either PATHS or an active control, which is a film-based intervention that provides general support to parents of GBA. The study condition is unblinded for both participants and the research team. Parent and child assessments will occur every 3 months over a 1-year period. Primary outcomes will be evaluated at 6 months after the intervention, and then, the control arm will crossover and receive PATHS, and dyads will be followed for another 6 months. This allows us to further test the effects of PATHS in the control arm while simultaneously modeling the longer-term effects at 9 and 12months in the original intervention arm.

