Parents who arrive at our website during the study are directed to a brief screening questionnaire that helps identify the most relevant resources for their family and also assesses their eligibility for this study. The automated screener directs only eligible parents to a prerecorded video featuring the study principal investigator ([name]) explaining the purpose of the study and procedures. Interested parents are then directed to the online REDCap (Research Electronic Data Capture; Vanderbilt University) system, a secure, web-based application for survey data collection [22]. Parents provide consent to participate, permission for their son (if he is younger than 18 years of age), and contact information for themselves and their son. Then, they complete their baseline assessment (preintervention) within the REDCap system. Upon completion of the parent assessment, sons are automatically contacted via email or text and invited to participate in an online questionnaire study about “how parents and sons discuss important topics.” Sons are not directly engaged in our intervention and are not informed of the nature of the intervention their parents will receive; these steps decrease GBA resistance to participation (eg, if they want to avoid talking to their parents about sex) and also reduce social desirability bias in their responses (ie, if they understood the intervention goals). Interested sons click a link directing them to the REDCap system, where they provide consent (or assent if younger than 18 years of age) and then complete the baseline assessment. Once parents and sons have completed their initial assessments, the study team receives an electronic alert notifying us that a family is prepared for enrollment in the RCT. At this point, we take a number of steps to ensure that parent-son dyads are legitimate and truly eligible: (1) we first review screener data to identify parents who have completed a screener more than once (eligibility criteria are not advertised, and parents complete the screener naïve to our criteria); parents who have completed the screener multiple times are ineligible unless data from the first assessment indicate that they have multiple children they might have screened for; (2) we next review responses from parent and son assessments to check for consistency (eg, age) and to ensure again that eligibility criteria are met (eg, to ensure that the son has not reported being HIV-positive); and (3) finally, we ask dyads to verify their identities in 1 of 2 ways: either uploading copies of their photo identification or participating together in a brief 5-minute video chat. Families for whom we have concerns about their authenticity or eligibility are required to participate in a video chat to provide clarification about the information they provided. Once verified, parents are considered formally enrolled in the RCT and randomized.

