**Condom access**					
	GBA^a^	Single item asking if the participant has possession of a condom (at home or elsewhere); if yes, a follow-up question requesting the upload of a photo of the condom in the participant’s hand.		BL^b^, 3, 6, 9, 12	
	Parent	Single item asking the parent if they know their son has possession of condoms.		BL, 3, 6, 9, 12	

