**Condom skills**					
	GBA	Condom use self-efficacy scale [44].		BL, 3, 6, 9, 12	
	GBA	Condom knowledge test (objective assessment of ability to differentiate correct and incorrect steps in using condoms from a list) [45].		BL, 3, 6, 9, 12	
	GBA	Video-recorded condom demonstration [47-49].		3, 9	

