## Discussion

### Potential Implications of Findings

GBA are the group of teens at highest risk for HIV infection in the United States, but evidence-based interventions to reduce that risk are extremely limited. If we demonstrate that PATHS reduces sexual risk behaviors or improves adolescent preparedness for sex, it will provide a new option for addressing an ongoing public health challenge. Additionally, to our knowledge, PATHS will be the first intervention for GBA that addresses a system of influence beyond the individual level. This is critical because not all adolescents are interested in engaging directly in HIV prevention interventions themselves. Having the option of reaching teens via their parents provides a valuable alternative for the field, ensuring that a greater number of adolescents have support for their sexual health.

This trial also aims to expand the field’s approach to assessing sexual health outcomes for adolescents. Clearly, the goal in any sexual health intervention is to reduce the incidence of poor health outcomes (STIs, HIV, and unplanned pregnancy). In the absence of extremely large samples and long follow-up periods, those outcomes will be difficult to detect among adolescents in any intervention trial. Thus, the widely accepted compromise has been to measure self-reported behaviors that are a clear part of the causal chain to incident disease or pregnancy (eg, condomless sex). However, those behavioral outcomes also carry limitations: self-reports are imperfect, and even when they are assessed reliably, those behaviors also must be common enough to create an opportunity for intervention effects to be observed. Often, the solution to the challenge of low behavioral frequency is for trials to recruit only GBA with histories of risk behavior or significant sexual experience. However, sexual health interventions might have different effects for youths who have already established patterns of sexual behavior, relative to youths who are less experienced. If trials preselect youths already engaging in risk behaviors, we will know less about intervention effects on GBA who have yet to initiate sex or sexual risk. Our approach in this trial is to test effects not only on self-reported behaviors but also on outcomes that can be reliably assessed in any adolescent (eg, photo-verified possession of condoms and demonstrated skill using a condom), regardless of their level of prior sexual experience.

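### The research team is declared unblinded with no exception for raters, so the video-recorded condom demonstration, the only performance-based skills measure, is open to detection bias

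*Protocol article*

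**What the plan says.** Under Methods, Study Design, the protocol article says: "The study condition is unblinded for both participants and the research team". No other section qualifies this for the scoring of outcomes.

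Table 1 (Measurement and timing of primary outcomes) gives three condom-skills measures, all from the son: a self-efficacy scale, a knowledge test that asks him to tell correct from incorrect steps in a list, and a video-recorded demonstration. The first two are collected at baseline and months 3, 6, 9 and 12. The demonstration is collected at months 3 and 9 only. For condom access, the son answers a possession item; "if yes, a follow-up question requesting the upload of a photo of the condom in the participant’s hand".

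Study Design also says: "Primary outcomes will be evaluated at 6 months after the intervention". The control arm then crosses over to PATHS.

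The Discussion (Potential Implications of Findings) notes that self-reports are imperfect. It then offers "photo-verified possession of condoms and demonstrated skill using a condom" as examples of outcomes that can be assessed reliably in any adolescent.

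On the sons, the Participants section says: "Sons are not directly engaged in our intervention and are not informed of the nature of the intervention their parents will receive". One stated reason is to reduce social desirability bias.

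**The concern.** Parents in a trial of this kind cannot be masked, and an open-label statement for them is unremarkable. Raters of recorded material are different: they can be masked without touching the intervention or the participants. The article describes the research team as a whole as unblinded, while one primary measure depends on a rater's judgement of how well a task was performed.

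That measure carries weight in the argument. It is the only condom-skills measure based on performance rather than on the son's own answers, and the Discussion relies on it to answer the weakness of self-report. If the rater knows the arm, a difference in demonstrated skill can be put down to lenient scoring, and the reliability claim is weakened where it is meant to be strongest.

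The design also guards against bias in the sons' responses by not telling them what their parents receive. Leaving the scoring of their recordings open sits badly with that care.

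**Working it through.** The plan states no figure on this point, so there is nothing to reproduce. The main check compares the sections; the arithmetic after it is illustrative.

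**Which measures need a rater**

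| Measure (Table 1) | Months | Rater judgement |
|---|---|---|
| Condom self-efficacy scale | BL, 3, 6, 9, 12 | None; answered by the son |
| Condom knowledge test | BL, 3, 6, 9, 12 | None; correct and incorrect steps picked from a list |
| Condom photo | BL, 3, 6, 9, 12 | Close to yes/no: is a condom in the hand? |
| Video demonstration | 3, 9 | Yes; quality of performance |

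The exposure is therefore essentially the video.

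**Which comparisons are exposed**

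- Month 3: PATHS against control before crossover. This is the only such comparison for the video. There is no baseline video, so no earlier score can be used for adjustment.
- Month 6: no video, so no score to bias.
- Month 9: the control arm has by then been given PATHS. The Limitations section plans a within-family comparison before and after crossover; for the video, that could only be month 3 against month 9 in the control arm. A rater who knows the wave could bias this too, so masking has to cover wave as well as arm.

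**How large the effect could be (illustration)**

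Assumptions, none of them from the documents: no true effect; a rater who favours one arm by a constant shift *d* in SD units; *n* scored videos per arm; an unadjusted two-sample z-test at two-sided 0.05.

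False-positive rate = Φ(δ − 1.96) + Φ(−δ − 1.96), with δ = *d* / √(2/*n*).

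Example: *d* = 0.1 and *n* = 100 give √(2/100) = 0.1414 and δ = 0.707. The rate is Φ(−1.253) + Φ(−2.667) = 0.105 + 0.004 = 0.109.

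| Assumed shift | n = 100 per arm | n = 150 per arm |
|---|---|---|
| 0.1 SD | 11% | 14% |
| 0.2 SD | 29% | 41% |
| 0.3 SD | 56% | 74% |

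The planned sample of 350 dyads gives 350/2 = 175 per arm. If every son supplied a video, the rates would be 15.5% at 0.1 SD and 46.5% at 0.2 SD. A larger sample makes a fixed bias more likely to reach significance, because the standard error shrinks and the shift does not.

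The false discovery rate adjustment in the Analysis Overview deals with multiplicity. It does not remove a systematic shift in one outcome.

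**The case against.** The strongest reply is that the central fact is inferred. The article never says who scores the videos or that those people know the arm. The sentence in Study Design is one line about the conduct of the trial and does not mention scoring. Coding procedures usually sit in a full protocol or manual, which is not shown, and their absence from a journal article is no fault. This stands in part: a reader might infer that unblinded staff score the recordings, and the documents do not establish that. It does not dispose of the point, which rests on what is stated. If coders are masked, the unqualified sentence is wrong and should be corrected; if they are not, the scoring should change.

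The reply also limits the scope, and here it is right. A reader might conclude that all the objective measures are exposed, or that the 6-month primary evaluation is biased. Neither follows. The knowledge test needs no rater, the photo check leaves little room for leniency, and the video is not taken at month 6. The video is one of three skills measures within one of several primary outcomes.

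Finally, the error rates rest on assumed shifts, assumed numbers of videos and a simpler test than the planned multilevel models. They show what a bias of that size would do and give no evidence that one exists. That is also correct.

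**Conclusion.** The point holds in a limited form. The unqualified statement that the research team is unblinded, set beside a primary measure that must be rated, leaves the only performance-based condom-skills score without stated protection from detection bias. The scores at risk are month 3, which is the sole randomised PATHS-versus-control comparison of this measure, and month 9 after crossover. This weakens the Discussion's claim that demonstrated skill can be reliably assessed.

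The conclusion depends on reading the research team as including the raters, which the article neither confirms nor excludes. It does not extend to the photo, the knowledge test or any 6-month value. The false-positive rates are illustrations in which both the shift and the number of videos per arm are assumed; they should not be read as estimates of bias in this trial. This is a worthwhile and inexpensive improvement, not a fault that undermines the primary evaluation as a whole.

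**What to change.** Reword the Study Design sentence to give blinding status separately for parents, sons, study staff and outcome raters. This would also reconcile its description of participants as unblinded with the Participants section, where sons are not told the nature of the intervention.

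For the videos, state that:

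- scoring follows a fixed checklist;
- scorers are existing team members masked to arm and wave who did not verify the dyad concerned. Verification is by photo identification or video chat, and a random file code does not mask a participant whom the scorer recognises;
- files carry random codes and are mixed across arms and waves;
- scores are completed before they are merged with allocation;
- any videos already scored unmasked are rescored in this way.

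The cost is file recoding and some rescoring time. No participant procedure changes and no new data are needed. The article projects that study activities will be complete by November 2026, with analysis and results in the first quarter of 2027, so masked scoring can be in place before the analysis. If coders are already masked, only the wording needs to change.

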### Participants

Intervention participants will be parents or legal guardians of GBA. Assessment participants will be the GBA sons of the parents enrolled. For inclusion criteria, we operationalize GBA as individuals ages 14-19 years, who are assigned male sex at birth, who identify their current gender as male, and who identify as some nonheterosexual orientation. Additional inclusion criteria include: parents and GBA must cohabitate at least 2 days per week (eg, parents with sons at college, or with irregular custody, will not be eligible), the participating parent must be aware of their son’s sexual minority identity, and GBA must report being HIV-negative or untested. Participation is open only to parent-son dyads in which both members agree to take part, and both must have the capacity to use an internet-enabled device. We will purposively recruit a sample that is at least 50% racial or ethnic minority GBA.

PATHS was created for parents of cisgender male youths, insofar, as it focuses on sexual behaviors that cisgender GBA might engage in and uses terminology that cisgender male youths typically use to describe their physical characteristics and sexual behaviors. Thus, our intention in excluding noncisgender youths was to ensure that the content was relevant to participating parents and to prevent the intervention from suggesting language to parents that would be inappropriate for use with adolescents of other gender identities. However, in the short time since we developed PATHS, adolescents’ understanding and use of gender terminology has evolved rapidly, with increasing number of youths describing their genders using more expansive terms (eg, genderqueer), while simultaneously experiencing little discordance between that identity and their physical sex characteristics (eg, an adolescent assigned male at birth, who identifies as genderqueer, but has no interest or desire in changing anything about their physical body to align with another sex). This became apparent as we initiated recruitment for the study and discovered that many parents identified their son’s current gender as “male” during screening, while the sons identified their gender using a more expansive term. Given this reality, we decided that PATHS would be appropriate for families in which a parent understands their son to be male, but their son identifies his gender more expansively, in the absence of any other indicator that he is on a developmental path toward making any kind of physical transition through gender-affirming care. Thus, we expanded our inclusion criteria to include youths who either (1) are assigned male at birth and identify as male or (2) are assigned male at birth, are identified by their parents as male, self-identify as some other gender, and report no interest in taking any action that would alter their body’s physical characteristics (ie, hormones and surgery).

Parents of GBA are recruited through a variety of means, building on strategies we have used previously to successfully recruit this population [20,21]. We maintain a website that serves as a platform for providing resources to parents of lesbian, gay, bisexual, and transgender youths who we are testing. We drive traffic to the site through multiple means. To advertise new studies, we use paid advertisements on social media platforms (Facebook and Instagram) aimed at specific demographic groups (eg, parents of teens). Additionally, we benefit from our historic work in this area over the past 10 years, as our website is now linked as a resource on other sites (eg, local PFLAG chapters and college counseling centers) that drive traffic to us each month.

Parents who arrive at our website during the study are directed to a brief screening questionnaire that helps identify the most relevant resources for their family and also assesses their eligibility for this study. The automated screener directs only eligible parents to a prerecorded video featuring the study principal investigator ([name]) explaining the purpose of the study and procedures. Interested parents are then directed to the online REDCap (Research Electronic Data Capture; Vanderbilt University) system, a secure, web-based application for survey data collection [22]. Parents provide consent to participate, permission for their son (if he is younger than 18 years of age), and contact information for themselves and their son. Then, they complete their baseline assessment (preintervention) within the REDCap system. Upon completion of the parent assessment, sons are automatically contacted via email or text and invited to participate in an online questionnaire study about “how parents and sons discuss important topics.” Sons are not directly engaged in our intervention and are not informed of the nature of the intervention their parents will receive; these steps decrease GBA resistance to participation (eg, if they want to avoid talking to their parents about sex) and also reduce social desirability bias in their responses (ie, if they understood the intervention goals). Interested sons click a link directing them to the REDCap system, where they provide consent (or assent if younger than 18 years of age) and then complete the baseline assessment. Once parents and sons have completed their initial assessments, the study team receives an electronic alert notifying us that a family is prepared for enrollment in the RCT. At this point, we take a number of steps to ensure that parent-son dyads are legitimate and truly eligible: (1) we first review screener data to identify parents who have completed a screener more than once (eligibility criteria are not advertised, and parents complete the screener naïve to our criteria); parents who have completed the screener multiple times are ineligible unless data from the first assessment indicate that they have multiple children they might have screened for; (2) we next review responses from parent and son assessments to check for consistency (eg, age) and to ensure again that eligibility criteria are met (eg, to ensure that the son has not reported being HIV-positive); and (3) finally, we ask dyads to verify their identities in 1 of 2 ways: either uploading copies of their photo identification or participating together in a brief 5-minute video chat. Families for whom we have concerns about their authenticity or eligibility are required to participate in a video chat to provide clarification about the information they provided. Once verified, parents are considered formally enrolled in the RCT and randomized.
